### 5.2 Study Procedures:

**Recruitment process:** Our recruitment and enrollment plan in the Minneapolis/St. Paul MN metropolitan area includes outreach, electronic, print, and social media to ensure we can enroll 180 participants to reach statistical power. (*Recruitment flyers and scripts uploaded as supplements.*) Depending on COVID-19 restrictions during enrollment, we are planning on collecting data either together in person with a research staff (which can happen at a clinic, another location of their choice, or at their home), or separately with the participants collecting data in their home, with research staff supporting them remotely by phone or by Zoom, as participants prefer.

**Enrollment visit (Visit 1):** The enrollment visit will take approximately 120 minutes. During the visit, bilingual (English and Hmong) researchers will review and discuss the study, consent form, and HIPAA form in participants' preferred language. Any questions will be answered, and the researcher will assess if potential participants understand what is expected of them before they sign the consent and HIPAA forms.

Once the consent form is signed, participants will complete questionnaires about their medical history, gout symptoms, lifestyle activities (including diet and tobacco, and exercise) and medication history (including prescription, over-the-counter medications, probiotics and herbal therapies). Researchers will measure anthropometry (height, weight, and waist- circumference), and vital signs (temperature, respiratory rate, oxygen saturation, blood pressure and heart rate).

**Trigger-food profiling:** Researchers will ask participants to identify their gout flare trigger foods, first by an open-ended question and then by reviewing a list of common trigger foods, developed with a Hmong registered dietician. We will ask if there is any known "amount" (dose) of the trigger food known to them and have them grade them as the "highest, moderate or lowest" association with triggering gout in them.

**Medication history:** Participants may be asked to bring their medications with them to the enrollment visit and may be asked about their adherence to these medicines. If

necessary, the researchers will ask for permission to get a current medication list from their medical clinic.

Gout Symptoms: The modified Gout Assessment Questionnaire 2.0^23 (modified by a cultural equivalent approach) and Swollen Joint Count (44 Joints) ([https://www.carearthritis.com/tools/tools\\_html.anonlaunch?toolid=8&refid=/physicians.php%23tab2](https://www.carearthritis.com/tools/tools_html.anonlaunch?toolid=8&refid=/physicians.php%23tab2) ) will be used.

Stool collection: Participants will be instructed in stool collection and will be given stool collection kits to take home with them for 2 consecutive days. They will return the samples at their convenience. Upon receipt at the study lab, the samples will be stored at -80°C until DNA extraction.

Blood collection: We will be offering two methods: 1) in person and 2) at home method. In person blood draws will be performed by a phlebotomist available at the visit and later for subjects who are not ready to consent at the visit but choose to consent later. Blood samples will be collected into serum collection tubes (BD 366668-1 Vacutainer® Plus Plastic Serum Blood Collection Tubes or equivalent) and stored at -20°C until testing. For at home blood collection, capillary blood collection tubes (Microvette® CB 200 uL or equivalent) will be available to participants for self-collection. After self-collection, participants will ship samples to [name]'s lab according to the regulation of Occupational Safety and Health Administration (OHSA) and Department of Transportation (DOT) to and stored at -20°C until testing.

We will test for serum urate and creatinine to assess kidney function (calculate eGFR), which is a confounding contributor to SU. Inflammatory markers link to gout and obesity will also be tested.

Viral serology (antibody test) related to SARS-CoV-2 will be tested using the method developed and validated at the Advanced Research and Diagnostic Laboratory (ARDL), University of Minnesota.

Saliva collection: DNA will be extracted from the saliva samples collected using a commercial collection kit. Genetic variants that are associated with HU, gout, the responses of ULT, or other medications which the participants may be taking during the study will be tested. Although others may be examined as this field of study evolves, some known examples of genes that will be assessed for genetic variations that impact either medications used or the conditions of HU and/or gout include *ABCG2*, and *SLC22A12*.

Urine collection: Participants will be asked to collect one urine sample during the visit. Urine urate and creatinine will be measured. Urine samples will be stored for additional analyses as needed.

**During the 8 Week of Study:** The bilingual (English and Hmong) researchers will contact each participant by phone (either text or phone call as participants desire) at **weeks 1, 4, and 7** during the study to assess any medication safety and tolerance issues, any

medication changes, and remind participants of the importance of precise timing of dosing leading up to final visit.

**Study Visit (Visit 2):** All the information collected in Visit 1 will be collected again at this visit except for informed consent, privacy statement, DNA and demographics. This visit will last approximately 120 minutes.

Table 1. Clinical data collected in each study visit

| Items                                                                   | Visit 1  | 4 Phone calls* | Visit 2  | Site** |
|-------------------------------------------------------------------------|----------|----------------|----------|--------|
| Informed consent and privacy statement (HIPAA)                          | X        |                |          | A/B    |
| Demographics                                                            | X        |                |          | A/B    |
| Anthropometrics: height, weight, waist circumference                    | X        |                | X        | A/B    |
| Medical history, including pregnancy status and COVID-19 vaccine status | X        |                | X        | A/B    |
| Medication and dietary history                                          | X        |                | X        | A/B    |
| Vital signs (BP, HR)                                                    | X        |                | X        | A/B    |
| Gout symptoms (GAQ2.0 and swollen joint count)                          | X        |                | X        | A/B    |
| Blood, saliva and urine samples collection                              | X        |                | X        | A/B    |
| Stool samples collection x 2 consecutive days                           | X        |                | X        | B      |
| Medication adherence                                                    |          | X              | X        | A/B    |
| Adverse effects from study medication                                   |          | X              | X        | A/B    |
| Blood samples: urate, creatinine, SARS-CoV-2 IgG analysis               | X        |                |          | C      |
| Saliva samples: DNA extraction and genotyping                           |          |                |          | D      |
| Urine samples: uric acid and creatinine analysis                        | X        |                | X        | C      |
| Stool sample: preparation and sequencing                                |          |                |          | D      |
| Length of visit                                                         | 120 mins | 5-10 mins      | 120 mins |        |

\* Four phone calls will be conducted at the end of week 1, 4, and 7.

\*\*Sites: (Locations of various activities/procedures)

- 1) A = Community-University Health Care Center (CUHCC-A1), the primary participating clinic site and/or Minnesota Community Care (MCC-A2) a secondary participating clinic/site.
- 2) B = Participants' home
- 3) C = Advanced Research and Diagnostic Laboratory (ARDL), University of Minnesota
- 4) D = University of Minnesota Genomics Center (UMGC) for genotyping samples

NOTE: In response to reducing risk for COVID-19 infection for study participants, all the activities conducted at A locations (the participating clinic sites) will also be offered as an option for no in-person contact at participants' home (B locations). Methods include phone/online interview (using REDCap to interview participants) or a phone/online hybrid (participant fills out questionnaires on their own using internet access or paper copies and recruiter/interviewer would be on phone for assistance). The collection of blood, saliva, urine, and stool will be performed by participants at their home. Once the samples have been collected, participants will contact research staff and research staff will go to participants' homes with personal protective equipment (PPE) including masks, shields, gloves, and gowns to collect the samples. During the collection process, support from research staff will be provided if needed through phone or Zoom per participants' preference.

*(Instrumental questionnaires, including demographic, medical, medication, dietary, gout symptoms questionnaires were uploaded as supplements.)*

The data repository center and clinical coordinating center will be located in [name] laboratory in University of Minnesota (UMN). [name] and co-investigators (specifically Drs. [name] and [name]) will review accrual, drop-outs, and any protocol deviations on a periodic basis (monthly or weekly depending on the criteria developed in our planned detailed monitoring schedule).

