## **13.0 Risks to Participants**

*13.1* Foreseeable Risks: Possible immediate risks could be associated biometrics measures, blood draws, stool collections, acute gout flare during the study period, side effects from vitamin C, and risk of genetic testing.

- As our study collects biometrics such as weight, height, and waist circumference, as a measure of obesity, participants may experience emotional upset upon learning the results of their obesity measurement.
- Risks associated with blood draws could include bruising, nausea, or fainting.
- When collecting stool samples by participants, skin contamination with feces from the collection container could happen.
- The intervention, vitamin C may not be sufficient to lower SU and prevent acute gout flare.
- Serious adverse reactions of vitamin C includes nephrolithiasis and hemolysis. Vitamin C can increase production of oxalate resulting in the deposition of oxalate within the kidneys and the formation of oxalate stones within the renal tract. Acute renal failure because of calcium oxalate crystals has occurred in several patients receiving a single intravenous dose of ascorbic acid, ranging from 2.5 to 60 g. Patients with glucose-6-phosphate

dehydrogenase deficiency following ascorbic acid administration have been reported with hemolysis.

- Risks related to obtaining genetic information
- Transmission of SARS-CoV-2 virus

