## **19.0 Provisions to Protect the Privacy Interests of Participants**

### *19.1 Protecting Privacy:*

Potential participants are encouraged to bring up questions and concerns about study participation. Participants are informed that participation is voluntary; they can refuse to answer any questions or complete any study activities if they feel uncomfortable, and that they may discontinue participation in the study at any time.

To protect the privacy of individuals who choose to participate in this study, testing (questionnaires, biometrics, and biospecimen collection) will be completed in a private space, away from other people. Only one researcher will be with the participant at the time of testing for privacy.

All enrollees will receive a unique study ID code. The study identification (ID) code is how all collected data will be recorded. Forms linking codes to personal identification information for all participants will be secured. All the data will be kept safe and under locked access during and after participants have completed the study based on the database protection policy described below. With study participants' permission for future contact, identifiers will only be available to the PI, the co-investigators, and select key personnel, such as a study coordinator. However, for participants who do not wish to be contacted for future studies, their data will be de-identified and identifiers will no longer be available to co-investigators.

*19.2* Access to Participants:

For participant safety and only with their permission, relevant medical records will be requested and reviewed for any adverse events reported by participants. Participants will be asked to sign a release authorization to grant access to these records. No other type of private records will be accessed for the study.

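### The only solicited adverse-event item is worded by attribution to vitamin C, so untoward events between visits may go unrecorded

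*Protocol*

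**What the plan says.** Protocol Section 5.2, Table 1, lists what is collected at each contact. Its one adverse-event row reads "Adverse effects from study medication" and is marked for the phone calls and for Visit 2. The only other row marked for the calls is medication adherence. The text on the eight-week period says that staff contact participants at weeks 1, 4 and 7 to "assess any medication safety and tolerance issues", to ask about medication changes, and to remind them about dosing.

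Elsewhere the protocol is wider:
- Section 18.3 says that harms or concerns of any kind that participants telephone in go into the monitoring reports and to the IRB.
- Section 19.2 says that, with permission, "relevant medical records will be requested and reviewed for any adverse events reported by participants".

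Section 13.1 lists acute gout flare during the study and side effects of vitamin C as separate foreseeable risks. On the latter it states: "Serious adverse reactions of vitamin C includes nephrolithiasis and hemolysis".

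For Visit 2, Section 5.2 says: "All the information collected in Visit 1 will be collected again at this visit except for informed consent, privacy statement, DNA and demographics". That includes the row "Medical history, including pregnancy status and COVID-19 vaccine status", the modified Gout Assessment Questionnaire 2.0 (GAQ2.0) and the 44-joint swollen joint count.

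**The concern.** An item limited to effects of the study medication asks someone, either the participant or a member of staff who knows the treatment, to decide on cause before the event is written down. Sections 4.1 and 5.1 describe an open-label study in which everyone takes vitamin C. With no untreated group, that decision is unreliable in an individual case.

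The information lost is of a kind that analysis cannot restore: an event never recorded cannot be reclassified later, whereas an unrelated event that was recorded can be set aside. It also matters for oversight. Section 18.3 plans no systematic review of data on untoward events and relies on reports reaching the investigators. What staff are told to ask therefore largely determines what the investigators can see. The primary endpoint, change in serum urate, is not affected.

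**Working it through.** No arithmetic applies. The protocol states no adverse-event rate and no share of events expected to be captured, so there is no figure to reproduce. The check sets the passages side by side.

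1. **What is solicited during treatment.** At the calls, Table 1 marks only adherence and the attribution-worded row. The call text is also framed by the medication, apart from the question on medication changes. The protocol contains no definition of an adverse event and no instruction to record first and judge cause afterwards. (The column is headed four calls while the text and footnote name three weeks; this point does not depend on which is meant.)

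2. **What the other sections accept.** Sections 18.3 and 19.2 place no condition of relatedness on a harm or adverse event. Both start from a report by the participant, and neither changes what staff ask. Section 5.2 is thus narrower than the sections that depend on it.

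3. **Gout flare.** Section 13.1 lists flare apart from the side effects of vitamin C and explains it as vitamin C perhaps not lowering urate enough. On that list, a flare is not an effect of the study medication, so a literal reading of the row leaves it out. GAQ2.0 and the joint count need no attribution, but Table 1 marks them only at Visits 1 and 2. They are symptom measures at two time points, not a dated record of flares.

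4. **Kidney stone.** Nephrolithiasis is named in Section 13.1 as a serious reaction but has no item of its own. It can be recorded through the attribution-worded row, the repeat medical history, a medication change mentioned on a call, or a spontaneous report.

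5. **Participants who do not reach Visit 2.** Section 12.2 stops data collection on full withdrawal. For these people the Visit 2 questionnaires do not exist, and the calls made before withdrawal are the only solicited source. Section 15.2 allows for 15% drop-out. If that occurred across the planned 180 it would be 0.15 × 180 = 27 people, though the protocol does not say how many would be full withdrawals.

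Every route that needs no attribution is therefore limited to Visit 2, indirect through a medication change, or dependent on the participant volunteering the event.

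**The case against.** The strongest reply is that a row label is not a question. The document contains no call script or adverse-event form, and Section 5.2 says that study questionnaires were uploaded as supplements. Staff may well ask more broadly than the label suggests. This stands as a limit on what can be concluded about practice, but the protocol as written does not tell staff to ask more broadly.

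A second reply is that several routes need no attribution: the repeat medical and medication history, GAQ2.0 and joint count at Visit 2; gout symptoms as a secondary endpoint in Section 3.2; medication changes asked about on the calls; the flare plan that each participant states at the start (Section 13.1); and spontaneous reports under Sections 18.3 and 19.2. This also stands. A reader might infer that nothing is recorded unless it is blamed on vitamin C, or that the named harms are certain to be under-counted. The documents support neither. They support only that recording may be incomplete, mainly for events that resolve between visits.

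A reader might also add acute renal failure and hemolysis as examples. Section 13.1 describes renal failure after single intravenous doses, whereas this study gives tablets, and hemolysis does not resemble gout. The protocol also does not say that stones would be mistaken for the participants' own disease; the stone example rests on the absence of a dedicated item, not on resemblance.

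Finally, an all-cause count without a comparator cannot isolate the effect of vitamin C either. That is correct. The case for an all-cause count is completeness: it does not depend on an individual causal judgement that this design cannot support.

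**Conclusion.** The concern holds as a wording fault with a practical consequence. The one solicited adverse-event item in Section 5.2 is conditioned on attribution to vitamin C, which is narrower than Sections 18.3 and 19.2. In an open-label study with no control arm, flares, stones and other untoward events between visits may go unrecorded. The other routes reduce the gap but leave it open.

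The size of any under-count is unknown. A reader might want to put a number on it by assuming a true risk and an attributed share. Both would be invented, and the protocol plans no safety rate or interval to which such a figure could apply. The conclusion rests on reading the row and the call sentence literally, and on no broader script being in use. It is a change worth making because it is cheap and improves safety capture; it casts no doubt on the primary analysis.

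**What to change.** In Section 5.2, reword the Table 1 row and the sentence on the phone contacts to cover *all adverse events, whether or not thought related to vitamin C*. Ask in the same words at each scheduled call and at Visit 2. Record onset date and seriousness for each event, and judge relatedness as a separate item once the event has been recorded. If a supplementary script or form already does this, cite it in Section 5.2. Section 5.2 would then agree with Sections 18.3 and 19.2.

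The cost is a change to one table row, one sentence and the matching form or script, plus a few minutes per contact. The downside is that more unrelated minor events will be recorded.

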#### 5.3 Study Duration:

- The duration anticipated for an individual participant's participation in the study is 8 weeks.
- It is anticipated that recruitment and intervention would take between 6 and 12 months.
- Laboratory and data analysis are anticipated to be completed within 2 years.

5.4 Use of radiation: This research does NOT involve the use of radiation.

5.5 Use of Center for Magnetic Resonance Research: This research will NOT involve the Center for Magnetic Resonance Research facilities.

## 6.0 Data and Specimen Banking

### 6.1 Storage and Access:

The study consent form provides participants the **option** to agree for use of their samples in future research. For those participants who agree, any stool, urine, or blood samples remaining after analysis is complete will be stored in secured UMN -80 freezers for future studies.

Identifiers will be available only to the research team throughout the duration of the data collection period, in order to contact participants for safety and

adherence. At the end of the data collection period, the map between participants' identifiers and their unique study ID will be maintained on a full-disk encrypted secure server behind the UMN firewall, with access only by the PI and co-Is. Identifiers will only be accessed again at the time of the dissemination event, when invitations to the participants and the broader community will be sent out to share the results of the study.

Once data is entered into the database, hard copy (paper versions of) surveys will be stored in a locked file cabinet of the PI's locked office in a secure UMN building. These paper surveys will be maintained until the results of the study are published, at which point they will be securely disposed.

The digital data for this study will be entered into a REDCap database, which uses a MySQL database via a secure web interface with data checks used during data entry to ensure data quality. REDCap includes a complete suite of features to support HIPAA compliance, including a full audit trail, user-based privileges, and integration with the institutional LDAP server. The MySQL database and the web server will both be housed on secure servers operated by the University of Minnesota Academic Health Center's Information Systems group (AHC-IS). The servers are in a physically secure location on campus and are backed up nightly, with the backups stored in accordance with the AHC-IS retention schedule. Backup tapes are stored offsite. The AHC-IS servers provide a stable, secure, well-maintained, and high-capacity data storage environment, and both REDCap and MySQL are widely-used, powerful, reliable, well-supported systems. Access to the study's data in REDCap is restricted to the members of the study team by username and password.

Participant accrual data will also be entered into OnCore as required by the University of Minnesota's Academic Health Center. OnCore is a suite of clinical and translational research modules consisting of software for research, patient registry, and biospecimen management.

The AHC IE will not be used for data and BioNet will not be used for any specimens.

